### Outcome and impact evaluation (Objective 1)

Two sub-objectives will be addressed in the impact evaluation: (1.1) evaluate the effect of the intervention on contraceptive stock availability in SDPs, and (1.2) examine the effect of changes in stock availability on the MCPR at the population level. Table 1 presents the key outcome and impact indicators used for objective 1, based on data collected by two studies.

**Table 1 Tab1:** Indicators used for outcome and impact evaluation

Indicator	Data source
1. Stock availability in SDPs^a^	
Percentage of SDPs with all methods available on a given visit (%)	SDP survey; Service Provision Assessments [46]
Percentage of SDPs with each of the most popular short-, medium- and long-acting methods available on a given visit (%)	SDP survey; Service Provision Assessments
Percentage of the month/year stocked-out for any method (%)	SDP survey; Service Provision Assessments
Percentage of the month/year stocked-out for the most popular short-, medium- and long-acting methods (%)	SDP survey; Service Provision Assessments
Percentage of SDPs experiencing any contraceptive stock-out since intervention roll-out (%)	SDP survey
Average duration of stock-outs	SDP survey
2. FP^a^ consultations	
Monthly number of FP consultations	SDP survey
Monthly number of FP products distributed	SDP survey
Percentage of long-acting methods among monthly FP products distributed (%)	SDP survey
3. Contraceptive use	
Percentage of WRAU^a^ using a modern method^b^ of contraception (%)	Demographic and Health Surveys [48]
Percentage of single, sexually active WRA^a^ using a modern method of contraception (%)	Demographic and Health Surveys
Percentage of WRAU with an unmet need for FP (%)	Demographic and Health Surveys
Percentage of modern contraceptive users using a long-acting method^c^ (%)	Demographic and Health Surveys

^a^
*SDP* Service Delivery Point; *FP* family planning; *WRAU* Women of Reproductive Age in Union; *WRA* Women of Reproductive Age

^b^Modern methods include condoms, pills, injectables, implants, intra-uterine devices (IUDs), sterilisation

^c^Long-acting methods include implants and IUDs

The first study will follow a non-randomised stepped-wedge design using secondary data. To determine the impact of the intervention on contraceptive stock availability (objective 1.1) we will use data from Service Provision Assessments [46], nationally representative surveys of health facilities conducted annually in Senegal.

A general mixed-effects logistic regression model will be constructed using an approach similar to the stepped-wedge analysis method outlined by Hussey and Hughes [47], although the rollout was not randomised. Stock availability will be modelled as a binary outcome variable (stock present or absent on the day of the survey) for all contraceptive methods, and as an ordinal variable for the number of each of the most popular short-acting (condoms and pills), medium-acting (injectables) and long-acting methods (implants and IUDs). Time will be treated as a fixed effect, and region as a random effect, to allow the intervention effect to vary regionally. Independent covariates at regional level, such as density of SDPs offering FP services and density of road network, will be used as well as SDP-level variables such as facility type.

Similarly, to examine the effect of the intervention on contraceptive use among WRAU (objective 1.2) we will use information on contraceptive use at the population level from the Demographic and Health Surveys [48], nationally representative surveys of women of reproductive age also conducted annually. As above, a mixed-effects logistic regression model will be built treating region as a random effect, and including woman-level covariates (such as education level) and regional covariates (such as pre-intervention MCPR). For both objectives, secondary analyses allowing for a delay in the effect of the intervention will be explored by allowing the variable for the intervention mode to be fractional.

The second study will be a 4-year monthly time series of contraceptive stock availability (objective 1.1) and FP consumption (objective 1.2), constructed from data from a sample of SDPs. Five of the 13 regions where the intervention was implemented by 3PLs (i.e. excluding Saint Louis) will be randomly selected, and 10 districts randomly selected in each region with probability proportional to the number of SDPs in the district. In each selected district, the health centre will be included, as well as three randomly selected health posts, for a total sample of 200 SDPs across urban and rural locations. There is limited guidance on sample size calculations for time series analysis, which usually focuses on the number of time points rather than of sampling units [49]. At least 48 monthly observations on stock inventory and FP consultations will be collected from each SDP, as well as from the selected district and regional storerooms, and the national-level storeroom, ensuring at least 24 monthly time points pre- and post-intervention.

Information on contraceptive stock availability will be extracted from stock cards, daily patient registers and stock journals, as well as for several ‘tracer’ stocks (anti-malarials, oral rehydration salts, amoxicillin, and iron tablets) not expected to change as a result of the intervention. Monthly number of FP consultations in which patients receive a contraceptive at the SDP will be extracted from patient registers. A time series analysis will be conducted by constructing a generalised linear segmented regression model of the probability of stock-out for any method on a given month, and for the most popular short-, medium- and long-acting methods. We will examine whether there is a change in the slope or level of the number of methods available and monthly FP consumption at SDPs between the pre- and post-intervention periods. This analysis will be repeated for the tracer stocks to compare their change in stock availability with FP methods as a proxy measure of the ‘normal’ distribution channels through which these commodities are still distributed.

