**Fig. 1 Fig1:**
[figure not shown]
Modern contraceptive prevalence rate and unmet need for family planning among women of reproductive age in union (WRAU) over time. Source: Demographic and Health Surveys [48]. Note: The red arrow denotes start of intervention rollout across regions (early 2013: Dakar, Thies and Kaolack regions; 2014: Diourbel, Kaffrine, Fatick, Saint-Louis, Matam and Louga regions; 2015: Tambacounda, Kedougou, Kolda, Sedhiou and Ziguinchor regions)

Supply chain management typically includes four main components: supply contract management; procurement; inventory management; and logistics and distribution. In most LMICs, supply chain systems for medicines are dominated by the Central Medical Stores model [10]. This model is both administratively and physically centralised, with procurement typically taking place at the national level, beyond which supply chains usually follow a country’s administrative structures, irrespective of country or population size [11].

“Push” and “Pull” are two primary mechanisms by which to distribute products to peripheral levels. A push system is one in which a central or regional storeroom determines the quantities of medicines to be ordered nationally and issued to each lower-level facility, based on population estimates, previous demand, and stock availability at the central level. While a push system can lead to more equitable rationing in the event of stock scarcity, it can result in stock-outs and wastage of products if forecasting at the central level does not take into account variation in need at the peripheral level. In contrast, a pull system is based on consumption data (demand) to determine the stock quantity to be ordered from a higher-level storeroom, thereby relying on decision-making at lower levels of the system. Pull systems are thought to allow for a more efficient distribution of medicines within the supply chain system, reducing the quantity of standing stock at any time and therefore of product wastage.

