### Design of the intervention – “the Informed Push Model”

The health system structure in Senegal follows a hierarchical model, with procurement centralised at the national level. Each of the 14 regional medical offices is responsible for overseeing the health districts within the region. Health districts typically include one health centre in the main town, as well as a network of predominantly rural health posts [37].

*The current supply chain model* (Fig. 2) is used to distribute most non-contraceptive medical commodities in Senegal, and is run by the central Senegalese supply programme (Pharmacie Nationale d’Approvisionnement, or PNA). Public Service Delivery Points (SDPs, i.e. health centres and health posts) submit stock requests to the district, which sends an aggregate order to the regional storeroom. Regional storerooms send aggregate orders to the national supply program, and after receiving supplies, prepare them for collection by the districts. Each SDP is then responsible for collecting their order from the district storerooms.

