## Methods

### Study setting

Senegal is a West African country with a population of approximately 14 million. It is classified as a lower-middle income country, with a Human Development Index rank of 163 out of 187 countries in 2013 [42]. Reproductive data are available from the 2014 Demographic and Health Survey [43], however we use data from the 2012–13 survey here to describe the context at the start of the intervention implementation. In Senegal, half (47 %) of women aged 25–29 were married at age 18 or below in 2012–13 [44]. The total fertility rate was 5.3 children per woman, with an average of 4.1 for women living in urban areas and 6.3 in rural areas [45]. Following the slow rise in modern contraceptive use reaching 12 % of WRAU in 2010–11, the MCPR increased to 16 % by 2012–13 (Fig. 1). An estimated 29 % of WRAU still had an unmet need for FP in 2012–13, implying that almost one third of women in union who did not want to get pregnant within the next 2 years were not using contraception [45].

Sharp differences existed in the MCPR between urban and rural areas (27 % compared to 9 %, respectively) and across educational levels (29 % among WRAU with secondary education and above, compared with 12 % among WRAU with no formal education). The most popular contraceptive method was injectables, accounting for 39 % of modern contraceptive users, followed by the pill (32 %) and implants (17 %) [45]. The public sector supplied the vast majority of contraceptives, with 83 % of modern contraceptive users obtaining their last method in a public SDP, and above 90 % for injectables and IUDs. The private sector supplied 13 % of users (predominantly condoms and pills) [44].

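### Region enters the stepped-wedge models as a random effect although rollout order was not randomised, so stable early-versus-late differences can leak into the intervention effect, mainly for stock availability

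*Protocol article*

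**What the plan says.** The section on the outcome and impact evaluation (Objective 1) takes a standard stepped-wedge mixed logistic model and notes that it is used "although the rollout was not randomised". For stock availability it states: "Time will be treated as a fixed effect, and region as a random effect, to allow the intervention effect to vary regionally". For contraceptive use, "a mixed-effects logistic regression model will be built treating region as a random effect".

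Protection against level differences between regions comes from covariates. The stock model names, as examples, the density of facilities offering family planning, road density and facility type. It names no pre-intervention stock level. The use model names education and "regional covariates (such as pre-intervention MCPR").

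The number of clusters is in the section on the design of the intervention: "Each of the 14 regional medical offices is responsible for overseeing the health districts within the region". The note to Fig. 1 gives the order: "early 2013: Dakar, Thies and Kaolack regions; 2014: Diourbel, Kaffrine, Fatick, Saint-Louis, Matam and Louga regions", then the remaining five regions in 2015. The Discussion relies on this staggering to attribute the effect.

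**The concern.** A random region intercept treats each region's level as a draw that is independent of when the region crossed over. Randomising the order would justify that; here the order was chosen. The random-effects fit then combines two sources of information: change within regions, and differences in level between regions exposed for longer and for shorter. Only the first is protected against stable regional differences.

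The weight on the second source grows as region-year cells get smaller. The facility survey behind objective 1.1 is therefore the exposed analysis.

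The stated reason for the choice, letting the intervention effect vary by region, does not require a random intercept. A random intercept does not deliver it; a random intervention slope does, and that can stand beside fixed region intercepts.

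**Working it through.** The article gives no sample size, power or regional levels for this analysis, so there is no figure to reproduce. The check asks how much of a stable first-wave gap appears as effect when the true effect is zero.

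**From the article:** 14 regions; waves of 3, 6 and 5 starting in 2013, 2014 and 2015; annual surveys.

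**Assumed:** 15 or 28 facilities per region-year (m); availability p = 60 %; between-region SD τ of 8 or 10 points; surveys 2012–2015 (T = 4) or 2012–2016 (T = 5). For MCPR: 570 women per region-year and p = 16 %.

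**Model (linear approximation on region-year means):** fixed time, random region intercept with variance τ², cell variance σ² = p(1−p)/m. Generalised least squares weights between-region against within-region information by ψ = σ²/(σ² + Tτ²). A stable gap contributes nothing within regions, so

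- leakage = ψB_xy / (W_xx + ψB_xx)
- SE ratio, fixed over random = √(1 + ψB_xx/W_xx)

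**Design terms, T = 4.** Exposed fractions are 0.75, 0.50 and 0.25, with mean 6.5/14 = 0.464.

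- B_xx = 4(3×0.286² + 6×0.036² + 5×0.214²) = 1.929
- B_xy = 4×3×0.286 = 3.429
- Total after removing time = (3×11 + 9×5)/14 = 5.571
- W_xx = 5.571 − 1.929 = 3.643

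**T = 5**, by the same steps: B_xx = 1.543, B_xy = 3.429, W_xx = 4.029.

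**Upper end (m = 15, SD 8, T = 4).** σ² = 0.24/15 = 0.016. ψ = 0.016/(0.016 + 4×0.0064) = 0.385. Leakage = 0.385×3.429/(3.643 + 0.385×1.929) = 0.30. SE ratio = 1.097.

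**Lower end (m = 28, SD 10, T = 5).** σ² = 0.24/28 = 0.00857. ψ = 0.00857/(0.00857 + 5×0.01) = 0.146. Leakage = 0.146×3.429/(4.029 + 0.146×1.543) = 0.118. SE ratio = 1.028.

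| m | SD (points) | T | Leakage | Bias from a 15-point gap (points) | SE random / fixed (points) |
|---|---|---|---|---|---|
| 15 | 8 | 4 | 0.301 | 4.5 | 6.04 / 6.63 |
| 15 | 10 | 4 | 0.234 | 3.5 | 6.18 / 6.63 |
| 28 | 8 | 4 | 0.208 | 3.1 | 4.56 / 4.85 |
| 15 | 8 | 5 | 0.252 | 3.8 | 5.93 / 6.30 |
| 15 | 10 | 5 | 0.189 | 2.8 | 6.03 / 6.30 |
| 28 | 10 | 5 | 0.118 | 1.8 | 4.49 / 4.61 |

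With fixed region intercepts, or with the region-mean exposure term, leakage is 0 in every row and the SE is the fixed-effect one.

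**Why SD 8 to 10.** A 15-point gap in 3 of 14 regions alone produces an SD of 15√(3/14 × 11/14) = 6.2 points, so a smaller SD would contradict the gap. At SD 5, m = 15 and T = 4, leakage is 0.44 and the SE cost 15 %, but only a smaller gap fits that SD.

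**MCPR (m = 570, SD 8, T = 4).** σ² = 0.1344/570 = 0.000236. ψ = 0.0091. Leakage = 0.0091×3.429/(3.643 + 0.018) = 0.0085. Even an 18-point gap gives 18×0.0085 = 0.15 point. At SD 10 it gives 0.10 point.

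**Logit-scale check.** Assume baselines of 27, 15 and 9 % by wave, a residual region SD of 0.3 on the logit scale, a true OR of 1.0 and surveys 2012–2015. The closed form then gives a spurious OR of 1.54 at 10 units per cell, 1.24 at 30 and 1.03 at 300, and 1.00 at every size with fixed effects. In a small simulation (25 replicates per setting), a baseline level measured with the same sample size removed only about 10 to 37 % of the leakage.

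**The case against.** **The only documented level difference concerns another outcome and another contrast.** The Study setting section says "Sharp differences existed in the MCPR between urban and rural areas" (27 % against 9 %). That is MCPR by residence, not stock by wave, and MCPR is where the bias is negligible. This stands: the stock gap used here is hypothetical.

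**The covariate lists are open and may absorb part of the gap.** True, but the named ones do not include a pre-intervention stock level, and a noisy baseline removes only part of the leakage.

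**Objective 1 has a second analysis.** The monthly segmented time series with tracer commodities does not depend on this model. It is a useful cross-check, but it does not correct the stepped-wedge estimate.

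**The bias is smaller than the standard error.** In the table it is about 0.4 (1.8/4.49) to 0.75 (4.5/6.04) of one standard error. That is not alarming, but it is systematic and avoidable.

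A reader might also infer that adjusting for pre-intervention MCPR puts the same survey rows on both sides of the model, or averages different calendar years for early and late regions. The article does not say how that covariate is built, so this cannot be held against it.

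**Conclusion.** The point holds in a limited form. The article fixes a random region effect under a rollout it says was not randomised, and the named covariates do not restore the missing independence between regional level and timing. For stock availability about 12 to 30 % of an unexplained first-wave gap would enter the effect, or roughly 2 to 4.5 points for a 15-point gap. This rests on assumed facility numbers, availability, between-region SD and survey years. For MCPR the leakage is about 1 % or less.

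Two stronger readings are not supported. One is that the urban-rural MCPR difference shows a biased contraceptive-use estimate; the arithmetic shows the effect there is negligible. The other is that the intervention will look better than it is because Dakar went first. The article gives no stock levels by region, and its pre-intervention figures for two Dakar districts (injectables out of stock on 43 % of days, implants on 83 %) show that early regions need not have started ahead. The direction is unknown. This is a cheap improvement to the analysis, not a fatal flaw.

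**What to change.** In the stock-availability model, and for consistency in the MCPR model, either enter one fixed intercept per region, or keep the random region effect and add the region's mean exposure as a covariate (Mundlak term). The two gave the same effect estimate and SE in the linear check above. If regional variation in effect is wanted, add a random intervention slope and say so explicitly.

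Under fixed intercepts, time-constant regional covariates such as road density or pre-intervention MCPR have no main-effect coefficient and serve only as effect modifiers. The Mundlak version keeps them.

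Cost: rewording of the analysis and no new data. The SE rises by about 3 to 10 % for the facility survey under the assumptions above (up to 15 % at 15 facilities and SD 5), and by under 1 % for the household survey. Neither version removes differences in trend between regions, which should be stated as a remaining limitation.

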There are several limitations to our approach. First, our ability to investigate contraceptive stock supply over time relies on the availability of good quality stock data in SDPs. Between 2010 and 2012, health staff in some regions of Senegal took strike action which manifested as a refusal to send health data to the district level, which may affect data availability for the time series study in regions where the 24-month pre-intervention period includes 2011–2012. Health facility and staff adherence to the strike was variable, and it is unclear whether stock data were particularly affected since a different cadre of staff (community-funded “dépositaires”, or stockists) is tasked with completing stock cards, rather than the centrally-funded nursing staff who were on strike. In addition, it is not clear whether, given the duration of the strike, data continued to be collected but were not sent upward or whether nursing staff and stockists stopped recording data in SDPs. The availability of good data in SDPs will be explored in the data quality pilot study prior to collecting data for the time series.

Second, estimating the contribution of the intervention to any observed increase in contraceptive use may be challenging given that other FP-related activities such as demand-generation activities, public endorsements of FP by community leaders, and outreach activities are implemented throughout the country. The evaluation methodology is designed to take this limitation into account as effectively as possible. The staggered rollout of the intervention across regions will enable us to estimate more precisely the effect attributable to the intervention. As part of the assessment of contextual factors (objective 3), we will further estimate the implementation intensity of FP-related activities in order to disentangle the potential effect of the intervention and of other FP-related activities on the MCPR.

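### The stepped-wedge models assume one common time path for all regions although rollout order was not randomised; for MCPR no stated analysis tests or relaxes this, and the attribution claim rests on it

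*Protocol article*

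**What the plan says.** The Protocol article, under Outcome and impact evaluation (Objective 1), adopts a published stepped-wedge analysis method for the facility survey data, "although the rollout was not randomised". The stock model is specified as follows: "Time will be treated as a fixed effect, and region as a random effect, to allow the intervention effect to vary regionally". The clause that matters here is "Time will be treated as a fixed effect"; no region-by-time term is stated beside it. For contraceptive use the text refers back to that description: "a mixed-effects logistic regression model will be built treating region as a random effect", with woman-level covariates and "regional covariates (such as pre-intervention MCPR"). The one secondary analysis named for these two models is a fractional intervention variable, to allow for a delayed effect.

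The caption of Fig. 1 gives the order of rollout: "early 2013: Dakar, Thies and Kaolack regions; 2014: Diourbel, Kaffrine, Fatick, Saint-Louis, Matam and Louga regions; 2015: Tambacounda, Kedougou, Kolda, Sedhiou and Ziguinchor regions". That is 3, 6 and 5 regions.

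The limitations in the Discussion accept that other family planning activities make attribution difficult. The first answer given is: "The staggered rollout of the intervention across regions will enable us to estimate more precisely the effect attributable to the intervention".

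**The concern.** A shared time effect plus regional terms identifies the intervention effect by comparing regions already exposed with regions not yet exposed in the same period. Randomised order makes the two sets comparable in expectation, in trend as well as in level. Here the order was chosen, so the comparison is fair only if the regions would have followed parallel paths without the intervention.

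None of the stated terms protects against unequal paths:

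- Pre-intervention MCPR, facility density and road density are regional levels. They do not adjust for differing slopes.
- A random effect for region, even if it also varies the intervention effect, leaves the underlying time path common to all regions.
- The fractional intervention variable changes the shape of the effect, not the untreated trend.

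Parallel paths cannot be taken for granted. National MCPR was rising before rollout, other programmes were running, and "Sharp differences existed in the MCPR between urban and rural areas". At stake is the main attribution claim for contraceptive use, and the cost-effectiveness ratios that take their effect estimates from Objective 1.

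**Working it through.** The article gives no numerical target for the stepped-wedge analysis, so there is no figure to reproduce. The check asks what the planned structure returns when the true effect is zero and underlying growth differs by rollout group.

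**From the article**
- 14 regions, rolled out 3/6/5 in 2013/2014/2015 (Fig. 1 caption).
- National MCPR 12 % in 2010-11 and 16 % in 2012-13 (Study setting): (16 - 12)/2 = 2 points per year.

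**Assumed, because the article does not say**
- Extra growth in the 2013 group of 1 or 2 points per year. The 2014 group has half of that (graded) or none (early only); the 2015 group has none.
- Which survey rounds enter the model.
- Whether exposure counts from the rollout year or the year after.
- One time effect per survey year.

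**Formula.** For exposure x in region i and year t, remove region and year means: r = x - mean(region) - mean(year) + overall mean. The estimate is sum(r × y)/sum(r²). A trend common to all regions cancels. An extra slope d in a group adds d × sum(r × (t - 2011)) over that group to the numerator.

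**Largest graded case:** rounds 2011 to 2015, exposure from the year after rollout. Sum(r²) = 4.029. The slope sums are +4.5 (2013 group), +3.0 (2014 group) and -7.5 (2015 group). With extra slopes 2, 1 and 0:

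(4.5 × 2 + 3.0 × 1)/4.029 = 12/4.029 = +2.98 points.

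**Lowest graded case:** rounds 2011 and 2013 to 2016, exposure from the rollout year. Sum(r²) is again 4.029. The slope sums are -1.671, +1.457 and +0.214:

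(-1.671 × 2 + 1.457 × 1)/4.029 = -1.886/4.029 = -0.47 points.

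**All layouts, graded growth.** False effect in MCPR points, for 1 / 2 points per year:

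| Survey rounds | Exposed from rollout year | Exposed from year after |
|---|---|---|
| 2011 to 2015, annual | +0.53 / +1.06 | +1.49 / +2.98 |
| 2011, 2013, 2014, 2015 | +0.32 / +0.65 | +1.38 / +2.76 |
| 2012 to 2015, annual | +0.06 / +0.12 | +1.12 / +2.24 |
| 2011, 2013 to 2016 | -0.23 / -0.47 | +0.72 / +1.45 |

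Random intercepts in place of fixed ones (variance ratio 5, assumed) change little: +3.08 instead of +2.98 in the largest case. The early-only pattern runs from -0.83 to +2.23. If the early regions grow more slowly, every sign reverses; for example, -1.49 replaces +1.49.

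**Logistic scale.** The planned models are logistic. With assumed 2011 levels of 16/11/10 %, a common rise of 1.5 points per year, rounds 2011 to 2015, exposure from the year after and graded growth, the null odds ratio is about 1.00 at 0.5, 1.03 at 1 and 1.10 at 2 extra points per year. The distortion is smaller because a point of growth moves the log-odds less from a higher level. A rise of 1.5 points per year is 0.015/(0.16 × 0.84) = 0.11 per year from 16 %, but 0.015/(0.10 × 0.90) = 0.17 from 10 %. Part of the early regions' extra growth in points therefore disappears on the log-odds scale.

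**With region-specific linear trends** the false effect in the linear model is 0.00 in every layout. This is exact only because the assumed differences are themselves linear.

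**The case against.** Most of the other side's case bears on how far the point reaches.

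- **This is a condensed article.** Trend checks are often left to an analysis plan, which may exist. That is fair, and absence alone would not be a finding. What remains is on the page: the stated model form, the statement that rollout was not randomised, and an attribution claim with no condition attached.
- **Nothing shows unequal slopes.** This stands. The urban/rural figures (27 % and 9 %) are levels at one time and are not split by rollout group; the national rise does not show regional divergence. The growth differences above are assumptions, and the 2-point case gives early regions an excess as large as the whole national rate.
- **There are partial safeguards.** The second study models pre-intervention slopes over at least 24 months and repeats the analysis on tracer stocks, for facility stock and consumption in five sampled regions. That partly covers stock availability but does not test the population MCPR model. Objective 3 measures the intensity of other programmes by region and stratifies results by it. That addresses one likely cause of divergence and asks whether the effect varies, but it does not adjust the time path.

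A reader might infer that faster growth in Dakar, Thies and Kaolack will be credited to the intervention, or that the plan has no check of trends at all. The article supports neither. It reports no regional trends, the direction of any bias depends on rounds and coding that it does not fix, and the time series study does look at pre-rollout slopes for stock.

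**Conclusion.** The point holds as a conditional one, and most strongly for MCPR (objective 1.2). Both stepped-wedge models assume a common time path on the log-odds scale that non-random rollout does not protect. For MCPR no stated analysis tests or relaxes it. For stock availability the check is partial.

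Under assumed graded differences of 1 to 2 points per year and no true effect, the linear model returns about -0.5 to +3.0 MCPR points (down to -0.8 if only the 2013 group differs), against a national rise of 4 points from 2010-11 to 2012-13. On the logistic scale the distortion is smaller, with null odds ratios of about 1.03 to 1.10 in the one layout tried and close to 1.00 at half a point per year. If regions share one path, there is no bias. The exposure is therefore material but unproven, which calls for a sensitivity analysis and a qualified claim, not a different main model.

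**What to change.** Keep the main model and add:

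1. A pre-declared sensitivity analysis, mainly for the DHS model of MCPR: the same model with region-specific or rollout-group-specific linear time trends, reported beside the main estimate.
2. A comparison of MCPR slopes by rollout group from the DHS rounds before rollout. Use lead terms only where enough pre-rollout rounds exist. The article dates only the 2010-11 and 2012-13 rounds before or around the first start in early 2013, so leads may not be estimable for the first group, and a null lead from so few rounds would be weak evidence.
3. In the Discussion, a condition on the attribution statement: it holds under common underlying trends and is supported only if the two models agree.

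The cost is analysis work on survey data already planned for use, and a wider interval in the sensitivity model. Regional trends can also absorb part of a delayed or growing effect, which the plan itself intends to explore. The trend model should therefore stand beside the main analysis and not replace it.
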